#### Harms

We will ask participants to report changes in health status, falls, fractures, or any other injuries. All serious adverse events will be reported to research ethics boards and the central coordinating site in accordance with their requirements.

### Recruitment and sample size

Our sample size for the current study was derived from an estimate of the required recruitment rate for the larger trial. For the future trial, a sample size of 54 in each of the intervention and control groups would allow us to detect between-group difference of two chair stands in the 30-s chair stand test with a standard deviation (SD) of 3.7 and power of 80%, which would be similar to what we have observed in prior studies of pre-frail older adults [28, 34], and is considered a minimal clinically important difference [35]. For the larger trial, we will inflate sample size by 15% to account for attrition, resulting in a sample size of 124 participants (~ 2 individuals per month, per site, across 5 sites over 13 months). To assess feasibility of recruitment in the current study, we plan to recruit 32 participants up to 5 months across 4 sites (8 participants per site). We chose a sample size of two individuals per site per month to retain the same recruitment rate as the future trial and allowed for an additional month of recruitment to be conservative. A sample size of 32 participants will also allow us to test the evaluation cut-offs for the feasibility outcomes of retention (min = 0.5, hypothesized = 0.80, required sample size = 19) and adherence (min = 0.5, hypothesized = 0.75, required sample size = 27) with an alpha level of 0.05 and power of 80% [36]. The minimal (min) values represent the lowest acceptable outcome for study feasibility, while the hypothesized values reflect the expected and satisfactory outcomes for success.

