### Primary outcome: feasibility

The feasibility outcomes are recruitment, adherence to the rehabilitation sessions, and retention. A future trial will be feasible if as follows: (a) we recruit eight people per site in 5 months, (b) adherence to the virtual rehabilitation sessions is 75%, (c) 80% of participants complete the trial. We will report recruitment as the number of participants recruited by each site, adherence as the proportion of scheduled virtual rehabilitation sessions participants attend, and retention as the proportion of participants who complete the final assessment out of the total number of participants. The exercise professional will record attendance to sessions.

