### Analyses

All analyses (Table 7) will be performed using SAS version 9.2 (Cary, NC, USA). The reporting is guided by CONSORT, SPIRIT, SAGER, and SIITHIA guidelines [37–39]. See Table 8 for Template for Intervention Description and Replication (TIDieR) checklist and Additional File 2 for SPIRIT checklist. Participant characteristics will be reported using mean (standard deviation (SD)), median (interquartile range (IQR)), or count (percentage). For the primary outcomes, we will report recruitment, adherence, and retention using count and percentage (95% confidence interval [CI]). We will use descriptive statistics and narrative or graphical means to report reach, effectiveness, adoption, maintenance, and resource use outcomes for quantitative data using an intention-to-treat approach and use content or reflexive thematic analysis for qualitative data [40]. We will report the between-group difference in effectiveness and maintenance outcomes as mean (SD) or median (IQR), percent change, and 95% CI. Analyses of between-group differences will be exploratory, and no clinical inferences will be made. There will be no interim analyses or stopping rules.

**Table 7 Tab7:** Variables, hypotheses, outcomes, and methods of analysis

Variable	Criteria for feasibility/hypothesis	Outcome measure	Methods of analysis
Primary feasibility outcomes			
Recruitment	We will recruit 32 participants, 8 per site, in 5 months	Number of participants recruited at each site	Descriptive statistics
Adherence	Adherence to the rehabilitation sessions will be 75%	The proportion of scheduled sessions participant attended	
Retention	80% of our sample will complete the trial	The proportion of participants who complete the final assessment out of the total number of participants	
Secondary clinical/implementation outcomes			
Reach	N/A	• Number of participants categorized by PROGRESS-Plus factors • Number of individuals recruited who are ≤ 12-week versus > 12-week post-vertebral fracture • Number of people who attend outcome assessments in-person versus virtually	Descriptive statistics and narrative or graphical means

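### The recruitment pass mark of 8 per site in 5 months is 1.6 per site-month, 16 to 20% below the main-trial rate it is said to retain; the extra month makes it lenient, not conservative

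*Protocol article*

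**What the plan says.** Recruitment and sample size (protocol article) sizes the pilot from the recruitment rate the larger trial will need. That trial is planned at 54 per group, inflated by 15% to 124, at about 2 "individuals per month, per site, across 5 sites over 13 months". For the pilot the section says "We chose a sample size of two individuals per site per month to retain the same recruitment rate as the future trial", and the same sentence adds that the authors "allowed for an additional month of recruitment to be conservative".

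The rule by which feasibility is judged includes that added month. Primary outcome: feasibility calls a future trial feasible if, among other things, "we recruit eight people per site in 5 months". Table 7 in Analyses has the same criterion: "We will recruit 32 participants, 8 per site, in 5 months". The Abstract and Introduction agree. Nowhere in the article is success judged at 4 months or on a monthly rate.

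**The concern.** The stated purpose of the pilot's size is to test whether sites can recruit at the pace the main trial depends on. Two per site-month is 8 in 4 months. Allowing 5 months for the same 8 lowers the rate that earns a pass, so the criterion no longer tests the rate it is said to retain. Extra time is cautious when planning a study, because it makes finishing more likely. In a success threshold it works the other way, because a slower programme can pass.

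Recruitment is one of three primary feasibility criteria. As written, the pilot could report recruitment as feasible at a pace that misses the main trial's own timetable, and nothing in the rule would reveal it.

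**Working it through.** **Inputs** (all from Recruitment and sample size, except the pass rule, which is from Primary outcome: feasibility and Table 7): difference 2 chair stands, SD 3.7, power 80%; 54 per group; 15% inflation; 124 participants, 5 sites, 13 months; pilot of 32 participants, 4 sites, 8 per site in 5 months. Assumption: two-sided alpha of 0.05 for the main trial. The article states alpha 0.05 only for the retention and adherence cut-offs.

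**1. The plan's own figures reproduce.**
- n per group = 2 × (1.960 + 0.842)² × 3.7² / 2² = 53.7, so 54.
- 108 × 1.15 = 124.2, so 124.
- 124 / (5 × 13) = 124/65 = 1.91 per site-month, which rounds to the stated 2.
- 2 per site-month × 4 months = 8 per site.

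**2. Rate implied by the pass rule.**
- 8/5 = 32/(4 × 5) = 1.6 per site-month.
- Against the exact rate: 1 − 1.6/1.91 = 16%.
- Against the stated rate: 1 − 1.6/2.0 = 20%.
- At 2.0 per site-month, 5 months would yield 10 per site (40 in total); at 1.91, about 9.5 per site (about 38).

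**3. What a bare pass means for the main trial.**
- Enrolled at 13 months: 1.6 × 5 × 13 = 104 of 124 (84%).
- Time to 124: 124/(1.6 × 5) = 15.5 months.
- Slack in the plan at 2.0 per site-month: 124/10 = 12.4 months, leaving 0.6 of a month.

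**4. Power, only if enrolment stopped at 13 months.**
- 104 × 0.85 = 88.4 analysed, about 44 per group.
- Two-sample t-test power: about 71% (normal approximation 72%). With 54 per group the same two methods give 79% and 80%.
- If enrolment continues to 124, slow recruitment costs no power.

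**5. Precision of the pilot's rate.**
- 32 recruits in 20 site-months, exact Poisson 95% interval: lower limit χ²(0.025; 64 df)/(2 × 20) = 1.09, upper limit χ²(0.975; 66 df)/(2 × 20) = 2.26.

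**6. How the rule behaves** (independent Poisson recruitment with equal site rates; my assumption, as the article gives no model).

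| True rate per site-month | 8 in 5 months: every site | 8 in 5 months: pooled 32 | 8 in 4 months: every site | 8 in 4 months: pooled 32 |
|---|---|---|---|---|
| 1.6 | 0.09 | 0.52 | 0.01 | 0.12 |
| 1.91 | 0.29 | 0.86 | 0.06 | 0.42 |
| 2.0 | 0.37 | 0.91 | 0.09 | 0.52 |

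**The case against.** **The extra month is disclosed and the arithmetic is right.** Both are true. Every figure reproduces, and the sentence that claims the same rate also announces the added month. This is a mismatch between a claim and a threshold. It is neither a calculation error nor something concealed.

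**The fifth month may be start-up time.** One idle month followed by 2 per site-month would give the main trial 12 × 5 × 2 = 120 of 124 in 13 months, a trivial gap. But the article describes the month as recruitment, and the rule cannot tell this pattern from a steady 1.6.

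**Read as a requirement on every site, the rule is not easy.** At a true 1.6, all four sites pass with probability of only about 0.09. This stands as a limit on the word lenient. The rule is lenient relative to the rate it claims to test, and in practice mainly if the pooled 32 is what counts. It also rules out the obvious repair: 8 at every site in 4 months would pass with probability of about 0.09 even at a true 2.0, so a simple tightening would usually reject a programme that recruits on schedule.

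**A pilot this small cannot separate 1.6 from 1.9.** Also true: the interval of 1.09 to 2.26 covers both. That is a reason to report the rate with its interval, not to describe the threshold as retaining the main-trial rate.

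**Stronger readings that the article does not support.**
- A reader might infer that main-trial power would drop to about 68%. That requires stopping at 13 months with 104 enrolled and also 20% attrition (83 analysed). The article states no such stop, and the attrition is a separate retention question.
- A reader might infer that reporting recruitment as a percentage with a confidence interval is invalid because the target is fixed. The article gives no denominator for that percentage. Numbers screened are collected, so enrolled out of screened is equally possible.
- A reader might infer that a pass shows the main trial cannot recruit. It shows only that 124 in 13 months from 5 sites has not been demonstrated; a bare pass is compatible with 124 in 15.5 months.

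**Conclusion.** The point holds as a moderate one. The pass rule of 1.6 per site-month does not retain the main-trial rate of 1.91 (stated as about 2), and conservative is the wrong word for an allowance that eases a success criterion. The gap is 16 to 20% and follows from the article's own figures without further assumption.

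The consequence at the threshold is a main trial of about 15.5 rather than 13 months, assuming 5 sites and a steady rate. The loss of power to about 71% is conditional on stopping at 13 months, 15% attrition and two-sided alpha of 0.05. The pilot's estimates and its participants are unaffected; what is affected is what a recruitment pass may be taken to show.

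**What to change.** Report recruitment as participants per site-month, overall and by site, with an exact Poisson 95% interval, and judge it against the 1.9 per site-month the main trial needs. Use the months each site was actually open to recruitment as the denominator, so that a site reaching its eighth participant early is credited with the faster rate.

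Then make the text consistent in one of two ways:

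1. Keep 8 per site in 5 months, delete the claim of an equal rate and the word conservative, and restate the main trial as 5 sites over about 16 months.
2. State that the rate is judged against 1.9 per site-month and that month 5 serves only to complete enrolment.

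The first leaves the success criterion untouched and costs a longer stated main-trial duration. The second keeps the 13-month plan and costs a slightly less favourable recruitment conclusion if the pilot only just reaches 32. Because it changes how a primary criterion of a registered trial is read, it should be documented as a change. Neither needs more participants. Both need each site's opening date and enrolment dates to be recorded; the article does not mention these, but they are simple to collect.

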### Analyses

All analyses (Table 7) will be performed using SAS version 9.2 (Cary, NC, USA). The reporting is guided by CONSORT, SPIRIT, SAGER, and SIITHIA guidelines [37–39]. See Table 8 for Template for Intervention Description and Replication (TIDieR) checklist and Additional File 2 for SPIRIT checklist. Participant characteristics will be reported using mean (standard deviation (SD)), median (interquartile range (IQR)), or count (percentage). For the primary outcomes, we will report recruitment, adherence, and retention using count and percentage (95% confidence interval [CI]). We will use descriptive statistics and narrative or graphical means to report reach, effectiveness, adoption, maintenance, and resource use outcomes for quantitative data using an intention-to-treat approach and use content or reflexive thematic analysis for qualitative data [40]. We will report the between-group difference in effectiveness and maintenance outcomes as mean (SD) or median (IQR), percent change, and 95% CI. Analyses of between-group differences will be exploratory, and no clinical inferences will be made. There will be no interim analyses or stopping rules.

**Table 7 Tab7:** Variables, hypotheses, outcomes, and methods of analysis

Variable	Criteria for feasibility/hypothesis	Outcome measure	Methods of analysis
Primary feasibility outcomes			
Recruitment	We will recruit 32 participants, 8 per site, in 5 months	Number of participants recruited at each site	Descriptive statistics
Adherence	Adherence to the rehabilitation sessions will be 75%	The proportion of scheduled sessions participant attended	
Retention	80% of our sample will complete the trial	The proportion of participants who complete the final assessment out of the total number of participants	
Secondary clinical/implementation outcomes			
Reach	N/A	• Number of participants categorized by PROGRESS-Plus factors • Number of individuals recruited who are ≤ 12-week versus > 12-week post-vertebral fracture • Number of people who attend outcome assessments in-person versus virtually	Descriptive statistics and narrative or graphical means
Effectiveness: physical function and balance, pain, fear of movement, falls (number of falls and number of people who fall), falls efficacy, quality of life, mood, physical activity, nutrition risk	Exploratory	• 30-s chair stand test, side-by-side stand, semi-tandem stand, tandem stand • Brief Pain Inventory Short Form • Tampa Scale of Kinesiophobia • Monthly falls survey • Short Falls Self-Efficacy • QUALLEFO-41 • Patient Health Questionnaire-8 • Physical Activity Scale for Elderly • SCREEN-14	Descriptive statistics and narrative or graphical means
Harms	No difference between groups	• Self-report of adverse events	Descriptive statistics
Adoption	Exploratory	• Number of screened and enrolled participants per referral source • The length of time to obtain radiology reports and number of people with ambiguous radiology reports	Descriptive statistics and narrative or graphical means
Implementation	Understanding the experiences of individuals involved in the study and adherence to the intervention sessions to inform future trials	• Semi-structured interviews with participants and exercise professionals • Proportion of prescribed exercises adhered out of the total exercises prescribed via the Wibbi app, reporting directly to exercise professional or a log • Fidelity	Reflexive thematic analyses for qualitative data Descriptive statistics and narrative or graphical means for quantitative data
Maintenance	Exploratory	• Adherence to the exercise sessions at the end of 18-week follow-up for immediate group only	Descriptive statistics and narrative or graphical means
Resource use	Exploratory	• Cost	Descriptive statistics

**Table 8 Tab8:** Template for Intervention Description and Replication (TIDieR) checklist for the VIVA feasibility study

Item category	Description
Brief name	Virtual Intervention for Vertebral frActures (VIVA): Feasibility Study for a Multicentre Trial
Why	Vertebral fractures are the most common fracture due to osteoporosis. Guidance on management suggests that a rehabilitation intervention should include pain management, nutrition, exercise, and safe movement strategies in people with a vertebral fracture; however, it is not clear if implementing the intervention may improve outcomes. Thus, there is a need to conduct a trial to determine if a future randomized controlled trial testing the effectiveness and implementation of such intervention is feasible
What: Materials	VIVA covers four areas: pain management, safe movement, exercise, and nutrition. The rehabilitation sessions led by an exercise professional tackle one of the four topics based on the need and preference of the participant. The intervention includes print and video resources and a framework for goal setting, selecting exercises, and teaching body mechanics • Participant’s handouts and videos: At the end of the sessions, each participant will receive resources based on the area covered during the session (e.g. the exercise professional provides the participant a one-pager that involves a guide to encourage adequate consumption of calcium, protein, and vitamin D) • Wibbi app: Exercise professional will deliver the resources and track adherence to the rehabilitation sessions and exercise programme using the Wibbi app • Zoom: The virtual meeting platform in which the study assessments and rehabilitation sessions will be conducted • Intervention manual: A manual provided to the exercise professionals that include detailed information on how to lead the rehabilitation sessions • Data collection manual: A manual provided to the research staff that include information on how to conduct day-to-day study procedures
What: Procedures	Exercise professional leads 1:1 once-weekly sessions (via Zoom or telephone) over 8 weeks. Sessions start with brief education on a topic (e.g. safe movement, pain management, exercise, nutrition), followed by training and modeling of exercise and safe movement strategies, then goal setting, and action planning. The exercise professional then prescribes resources
Who: Provided	Rehabilitation sessions will be delivered by an exercise professional who is a physical therapist, exercise physiologist, or kinesiologist
How	The sessions will occur via Zoom, but communication via telephone is an option if a participant cannot use Zoom, or based on participant preference. An exercise professional and participant will meet in a one-on-one format
Where	The rehabilitation sessions will occur at participant’s home with virtual support from exercise professional
When and how much	The participant and exercise professional will meet once a week for 45–60 min over 8 weeks. During each session, an exercise professional will create an action plan with the participant for the following week that outlines what, when, and how much to perform for each activity *Nutrition guidance* • Participants will implement the nutrition tips daily *Pain management strategies* • Participants will implement pain management strategies daily *Spine safe movement* • Participants will implement spine safe movements when performing daily activities *Exercise to improve strength and balance* • Depending on the time after fracture and patients’ needs, participants will perform the following categories of exercises three times a week o At least one exercise for back extensor muscles Intensity: 3–10 sets of 5–10-s holds or 2–3 sets of ~ 10–12 repetitions with at least 2–3 repetitions in reserve o One or more exercise for shoulder stabilizers Intensity: Two sets of 5–10-s holds or 2 sets of 6–10 reps, with at least 2–3 reps in reserve o Three exercises for balance Intensity: Three sets of 30 s or as many reps as possible in 30 s o Three or four exercises for lower body physical functioning Intensity: 2–3 sets of ~ 6–10 repetitions, ~ 2–3 repetitions in reserve o At least three exercises progressive resistance training Intensity: 2–3 sets of ~ 6–10 repetitions with 1–3 repetitions in reserve • Participants will be encouraged to perform light PA as tolerated and/or ≥ 20 min/day moderate physical activity as tolerated
Tailoring	The one-on-one format allows for tailoring the sessions based on different needs of each participant while considering their function and the status of the vertebral fracture. For the sessions involving exercise instruction, exercises are tailored to the participant’s abilities
Modifications	N/A
How well: Planned	With consent, we will record two sessions per site, selected at random, and complete a checklist to assess intervention fidelity. Exercise professionals will receive training and will be provided the intervention manual to ensure the rehabilitation sessions and study procedures adhere to the protocol

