## Methods

### Trial design

The trial is a four-centre, pragmatic [24] (Supplementary Table 1, Supplementary Fig. 1, Additional File 1) [25], pilot hybrid type 1 effectiveness-implementation trial with two parallel groups, randomized in a 1:1 ratio and stratified by centre in variable-sized blocks (ClinicalTrials.gov Identifier: NCT06650410). Participants will be randomized to the following: (1) immediate receipt of VIVA intervention or (2) wait-list usual care control and delayed receipt of VIVA 10-week post-randomization. The randomization sequence will be created and uploaded to REDCap by the trial statistician. Randomization will take place after the baseline assessment; the exercise professional delivering the intervention (not blind to allocation) will access the randomization function in REDCap to determine the participant’s allocation and communicate it to them. Outcome assessors will be blind to group allocation. Participants will not be blind to group allocation because they will know what group they are assigned to.

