### Data collection and management

The data will be managed using the REDCap electronic data capturing platform (https://www.project-redcap.org/). Assessments will be conducted by research staff at each site who are blind to group allocation; participants will be invited to complete assessments virtually but can choose to complete them in person if offered by the recruiting research site. Research staff at each site will administer physical assessments virtually at the Vancouver site, in-person at the Montreal site, and both in-person and virtual at the Hamilton and Toronto site. Participants will receive a link to the questionnaires via REDCap and complete them independently before the scheduled physical assessments, with the option to respond by mail or over the phone. Participants will complete physical assessments and questionnaires at baseline, 9 weeks, and 18 weeks after enrollment (Table 6 and Supplementary Fig. 2, Additional File 1). Each assessment will take approximately 45 min to complete. The exercise professionals will not be blind to group allocation, and may collect data on participant attendance, or adverse events (e.g. falls) reported to them during exercise sessions. Participants are free to withdraw anytime from the intervention, assessment, or both.

**Table 6 Tab6:** Study events and timeline

Activity		Staff member	Pre-randomization		W 1–8	W 9	W 10–17	W 18
All participants	Review eligibility criteria	Staff	X					
	Obtain consent to release medical records	Staff	X					
	Verify vertebral fracture using X-ray reports	Staff	X					
	Informed consent	Staff	X					
	Technology consultation	Staff		X				
	Demographic and medical history information	Staff blinded		X				
	Questionnaires	Staff blinded		X		X		X
	Physical assessments	Staff blinded		X		X		X
	Exit interview	Staff unblinded						X
	Adverse events, falls, fractures	Staff blinded			X			
Immediate VIVA delivery	Intervention session	EP			X			
	Practice continued behaviour change						X	
Delayed VIVA delivery	Intervention session	EP					X	
Other	Fidelity	Staff unblinded			X			
	Exit interview with exercise providers	Staff blinded						X

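### Randomisation is stratified by centre, but the exploratory between-group 95% CIs are described without a centre term; if centres differ, pooled intervals are somewhat too wide

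*Protocol article*

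**What the plan says.** Under Trial design, allocation is "randomized in a 1:1 ratio and stratified by centre in variable-sized blocks". Under Recruitment and sample size, "we plan to recruit 32 participants up to 5 months across 4 sites (8 participants per site"), which is about four per arm in each centre.

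Under Analyses: "We will report the between-group difference in effectiveness and maintenance outcomes as mean (SD) or median (IQR), percent change, and 95% CI". The same paragraph calls these comparisons exploratory and rules out clinical inference from them. In Table 7, the method given for the effectiveness outcomes is descriptive statistics with narrative or graphical presentation. Centre, a model or a covariate appears in neither place. Neither place says that the interval will be unadjusted.

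Under Data collection and management, the mode of the physical tests varies by centre: "Research staff at each site will administer physical assessments virtually at the Vancouver site, in-person at the Montreal site, and both in-person and virtual". The last phrase refers to Hamilton and Toronto. The participant's choice depends on the centre too: "participants will be invited to complete assessments virtually but can choose to complete them in person if offered by the recruiting research site".

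**The concern.** Stratifying by centre aims to make the arms nearly equal in their centre mix, so differences between centres largely cancel from the arm contrast. A 95% CI built from the two pooled arm SDs does not recognise this, because the SDs still contain the between-centre spread. The interval then covers more than 95% of the time and understates the precision that the design bought.

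Here there is a specific reason to expect centres to differ on the physical tests. At Vancouver and Montreal the centre determines whether a test is done by video or in person. The tests affected include the 30-s chair stand, which is used to size the future trial.

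With about eight people per centre, variable block sizes and some dropout, the arms may also not stay level within each centre. A centre difference can then enter the raw contrast by chance.

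The stake is modest. These measures are listed as potential effectiveness outcomes for the main trial, so their estimates and intervals will be read, even though no decision in this study depends on them.

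**Working it through.** **Inputs.** From the protocol article: SD 3.7 for chair stands, 32 participants, four centres, 1:1 allocation (16 per arm, four per arm per centre if exactly balanced). Assumed, because the documents do not give it: the share of total variance due to centre (ICC), varied from 0 to 0.20.

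**The plan's own figure.** The future trial is sized to "detect between-group difference of two chair stands in the 30-s chair stand test with a standard deviation (SD) of 3.7 and power of 80"%, giving "a sample size of 54 in each of the intervention and control groups". Check, with two-sided alpha 0.05 assumed:

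n per arm = 2 × (1.960 + 0.842)² × 3.7² / 2² = 53.7, rounded up to 54. The figure reproduces, so 3.7 is taken as the SD.

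**Half-width from pooled arms.** With four centres equally represented in each arm of m = 16, the expected within-arm variance is

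3.7² × [(1 − ICC) + ICC × (16 − 4)/(16 − 1)] = 3.7² × (1 − 0.2 × ICC).

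Half-width = t(0.975; 30 df) × 3.7 × √(1 − 0.2 × ICC) × √(2/16), with t = 2.042.

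**Half-width adjusted for centre.** Three further degrees of freedom are spent:

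Half-width = t(0.975; 27 df) × 3.7 × √(1 − ICC) × √(2/16), with t = 2.052.

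**Results, in chair stands:**

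| Assumed ICC | Pooled | Centre-adjusted | Pooled relative to adjusted |
|---|---|---|---|
| 0 | 2.67 | 2.68 | 0.5% narrower |
| 0.05 | 2.66 | 2.62 | 1.6% wider |
| 0.10 | 2.65 | 2.55 | 3.9% wider |
| 0.20 | 2.62 | 2.40 | 9.0% wider |

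The two are equal at an ICC of about 0.01.

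**Coverage.** In 20,000 simulated balanced trials per ICC, the pooled interval covered 94.9% at ICC 0, 95.7% at 0.10 and 96.3% at 0.20. The adjusted interval stayed near 95%.

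**Dropout.** The table assumes exact balance within centre. With 13 per arm, still balanced, the half-widths at ICC 0 are 3.00 pooled and 3.02 adjusted. When 6 of the 32 are instead lost at random (about 20%), the arms become uneven within centres and the adjusted estimate pays for that as well. Simulating this (20,000 trials per ICC), the adjusted interval is about 2% wider at ICC 0 and the two are about equal at ICC 0.05. The pooled interval is about 2% wider at ICC 0.10 and about 7% wider at 0.20.

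**The case against.** The strongest reply is that this reads too much into silence. The article says what will be reported, not how the interval is computed, and a full protocol or statistical analysis plan that is not shown may already include centre. It stands to this extent: nobody can say that the plan rules out adjustment. But the article does have a methods column for these outcomes, and what stands there is descriptive group summaries. The natural reading is a pooled comparison, which does not follow the factor used to randomise.

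Several stronger readings are tempting, and the documents do not support them:

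- **That the intervals are certainly too wide.** This needs a between-centre variance that the documents do not give. In the balanced simulations at ICC 0.05, the pooled interval was the wider one in only 52% of trials.
- **That centre fixes how the physical tests are done.** This is true at Vancouver and Montreal only. Hamilton and Toronto use both modes, so mode also varies within those centres.
- **That every effectiveness outcome is affected by mode.** The site rule concerns the physical tests. Pain, fear of movement, quality of life, mood, activity and nutrition risk come from questionnaires that participants normally complete themselves. For these, only case mix could make centres differ.
- **That the excess width is 2%, 5% and 11%.** This results from holding the pooled half-width at 2.67 at every ICC. The pooled width also falls slightly as the ICC rises, which gives 1.6%, 3.9% and 9.0%.

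It can also be objected that if 10% is read as the share of variance centre explains in the sample, rather than in the population, adjustment gains nothing: 2.55 × √(30/27) is about 2.68. That is correct, but it is a different quantity. Three centre terms out of 30 degrees of freedom explain 10% by chance alone, so an observed 10% corresponds to no true centre effect.

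Finally, the error is conservative, the comparisons are exploratory, and the future trial's SD comes from prior studies. All of this stands and limits the point to a minor improvement.

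**Conclusion.** The point holds as a minor, conditional one. The trial randomises within centre, and the article describes its exploratory between-group intervals without centre. If centres differ, those intervals are conservative. At full balanced follow-up the chair-stand half-width is larger by about 0.04, 0.10 and 0.22 stands at an ICC of 0.05, 0.10 and 0.20. With about 20% random dropout the gain from adjusting is smaller and starts only above an ICC of about 0.05.

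These sizes rest on an SD of 3.7, about 16 per arm, and an assumed centre share. A reader might infer that the feasibility conclusions or the future trial's sample size are put in doubt. They are not: recruitment, retention and adherence do not use these intervals, and the 54 per group does not depend on them.

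**What to change.** In the Analyses section, state that the between-group difference and 95% CI for continuous effectiveness outcomes are estimated from a linear model with arm and centre, and that raw mean (SD) per arm is kept as description. If an existing analysis plan already specifies this, the sentence simply brings the article into line with it.

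The cost is one sentence and a model term that uses data already held. Statistically it is three degrees of freedom: if centre has no effect, the interval is about 0.5% wider with 32 analysed and about 2% wider with 20% dropout. The change does not deal with mode differences within Hamilton and Toronto. The counts of in-person and virtual attendance that the article already plans to report should be read alongside the physical-test results.
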